The strong trend of early dialysis initiation for end-stage kidney disease (ESKD) patients over recent decades makes the burden even greater. Data from the United States showed that the proportion of new dialysis patients with glomerular filtration rate (GFR) ≥10 ml/min/1.73m^2^ increased rapidly from about 10% in 1996 to around 50% in 2008 [3]. Between years 2000–2004 and 2005–2009, mean estimated GFR (eGFR) at dialysis initiation increased from 9.8 to 11.0 ml/min/1.73 m^2^ [4]. Early dialysis initiation not only increases the cost of medical treatment but also has no additional benefit for patients in long-term outcomes. Observational data showed that the short-term or long-term survival was not affected for chronic kidney disease (CKD) patients with stable low GFR (≤5 ml/min/1.73m^2^, and even ≤2 ml/min/1.73m^2^) before dialysis treatment [5, 6]. A recent retrospective cohort study found no statistically significant survival difference for early compared with later dialysis initiation (interpolated eGFR at dialysis therapy initiation ≥10 ml/min/1.73m^2^ vs. < 10 ml/min/1.73m^2^) [7]. Furthermore, some data even showed that early initiation seemed to produce an additional burden to patients and the health care system [5, 6, 8]. The Initiating Dialysis Early and Late (IDEAL) study, the only RCT research on this issue, found that the all-cause mortality, comorbidities, and quality of life showed no difference between early (GFR 10–14 ml/min/1.73m^2^) and late (GFR 5–7 ml/min/1.73m^2^) dialysis starters [9]. However, this study is limited by the condition that the difference for average GFR between two groups (12 ml/min/1.73 m^2^ vs. 9.8 ml/min/1.73m^2^) was not great. Moreover, the achieved GFR were relatively high for both groups. Thus, several major renal organizations have reassessed the risks and benefits of the practice of initiating early RRT [10–14]. The Canadian Society of Nephrology released a clinical practice guideline in which an “intent-to-defer” approach for dialysis initiation and strategy to initiate dialysis in the absence of symptoms in patients with an eGFR of 6 ml/min /1.73 m^2^ or less was recommended [12]. In this guideline, the specialists also expressed that the optimal management of patients with an estimated GFR of 6 ml/min per 1.73 m^2^ or less was based on limited data. The updated KDOQI (Kidney Disease Outcomes Quality Initiative) guideline emphasized that the decision to initiate maintenance dialysis “should be based primarily upon an assessment of signs and/or symptoms … rather than on a specific level of kidney function in the absence of such signs and symptoms.” [14]

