#### Deferred Dialysis initiation group

In this intervention group, similar flow paradigm of clinical indicators (Fig. 2) for initiating dialysis are used. Researchers will not start dialysis treatment for patients who are asymptomatic until their eGFR is below 5 ml/min/1.73m^2^. If safe for patients, investigators will postpone dialysis as late as GFR 2 ml/min/1.7m^2^. Clinical indications for initiating dialysis are the same as listed above for the routine dialysis initiation group.

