### Statistical analysis

#### Sample size

In this study, a cluster randomized design is used. The primary endpoint of the study is death rate, which will be determined by survival analysis. According to the IDEAL study, the death rate was 37% during a median follow-up period of 3.59 years [9]. Because we include relatively stable patients the mortality rate may be lower; we assume the death rate will be 30% or less within 3 years. The project selection window for patient enrollment is 30 months. Sood et al. found an adjusted facility-level intraclass correlation coefficient (ICC) of 0.031 in their work [16]. We get 8 clusters per group. Scholars have proposed that a sample size calculated assuming individual randomization can be inflated by a Design Effect (DE) to reach the required level of statistical power under cluster randomization [17]: DE = 1+ (m-1) ρ, where m is the number of individuals per cluster and ρ is the ICC.

If we assume that alpha = 5%, (1-beta) = 80%, patients are assigned 1:1, a difference of 10% in death rates between these two groups is considered acceptable. We use log-rank tests to get the events (87 vs 57) with the Power Analysis and Sample Size Software, version 13 (NCSS, LLC. Kaysville, Utah, USA) and the number of individuals per group is 473. Thus, the number of total events under the consideration of cluster effects is 198 (128 vs 70). This is an endpoint driven study. We will complete the study when we get enough endpoint events, which is 198 events.

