#### Analysis

In this randomized controlled trial, equivalence tests for two proportions in a cluster-randomized design will be performed according to requirements in the CONSORT (Consolidated Standards of Reporting Trials) statement. Sociodemographic, clinical, and economic data will be analyzed per group.

Baseline characteristics at enrollment will be reported as the mean and standard deviation (SD) for continuous variables and percentage for categorical variables. Continuous variables not normally distributed will also be presented as a median and interquartile range.

Missing data will be imputed using multiple imputation regression methods.

Cox analysis will be used to compare all-cause mortality, acute nonfatal cerebro-cardiovascular events, and hospitalization before and after dialysis treatment between the two groups.

T-tests will be performed to compare nutritional status, quality of life, residual renal function (urine volume), and medical expenses based on a data-paired analysis (before-after study). Continuous data will be compared using a paired t-test if the variable is normally distributed or Wilcoxon test for non-parametric variables. The MacNemar test will be used for categorical variables (Fleiss test, if necessary).

Statistical significance will be considered at a value of *p* ≤ 0.05. All statistical analyses will be performed with SAS, version 9.4 (SAS Institute, Cary, NC; USA).

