Recently, the Canadian Kidney Knowledge Translation and Generation Network published its study protocol “Knowledge Translation Interventions to Improve the Timing of Dialysis Initiation: Protocol for a Cluster Randomized Trial,” which aimed to evaluate the efficacy and safety of a knowledge translation intervention to promote the intent-to-defer approach in clinical practice [20]. The study designs have some similar components. However, they are very different. The emphasis of the Canadian research is to determine whether active knowledge translation intervention can reduce early dialysis starts. However, our study aims at evaluating the efficacy and safety of early and late dialysis initiation and the influence of timing on subsequent clinical outcomes directly.

An endpoint event-based power estimation is adopted in this study. It will allow all sites to finish together and avoid trial power being affected by alterations in accrual times. It will also protect the study power from lower than predicted event rates.

We acknowledge the following study limitations: (1) The results of the randomized study have limited generalizability due to the healthier nature of patients who participate in trials; (2) There may be a tendency for patients enrolled in clinical trials to alter their behavior due to awareness of being observed [19]. Thus, all patients may have relatively better outcomes; (3) Although this is facility-level research aimed at avoiding experimental contamination, the facilities in the routine group may also adopt the strategies in the delayed group unintentionally; (4) Patients in the routine group may actively delay their dialysis due to poor financial conditions. Thus, the eGFR rates may be similar at the end of the study and may endanger the power of this study; and (5) Patients with financial problems (e.g. without medical insurance) in both groups may get suboptimal medical care, which may impact their outcomes.

Even if the eGFR values of patients in both groups at dialysis initiation are low and not sufficiently different, this study will still potentially have economic, health, and scientific implications. Completing this study will add new knowledge about the timing of dialysis initiation.

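### Under the planned equivalence test, convergence of eGFR at dialysis start favours a conclusion of equivalence, but the Discussion treats it only as a threat to power and still expects knowledge about timing

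*Protocol article*

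**What the plan says.** The Analysis section states that "equivalence tests for two proportions in a cluster-randomized design will be performed". The same section adds that "Cox analysis will be used to compare all-cause mortality, acute nonfatal cerebro-cardiovascular events, and hospitalization" between the groups, with significance at p ≤ 0.05. The Sample size section uses a log-rank calculation and says that "a difference of 10% in death rates between these two groups is considered acceptable". It does not label this figure as an equivalence margin.

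The arms differ only in the eGFR at which a patient without symptoms starts dialysis: 7 in the routine group, below 5 in the deferred group. For everything else, "Clinical indications for initiating dialysis are the same as listed above for the routine dialysis initiation group".

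The Discussion lists two ways in which the contrast may shrink. Routine facilities may take up the deferred approach without intending to, and "Patients in the routine group may actively delay their dialysis due to poor financial conditions". The only consequence it gives for similar eGFR is a danger to power. Its closing remark on this begins: "Even if the eGFR values of patients in both groups at dialysis initiation are low and not sufficiently different, this study will still". The rest of that sentence allows for possible value of an economic, clinical and scientific kind, and the next one expects a gain in knowledge about when to start dialysis. Elsewhere in the Discussion, the aim is described as the direct influence of timing on outcomes.

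The Background faults the earlier randomised trial on this ground: "this study is limited by the condition that the difference for average GFR between two groups" was not great (12 versus 9.8 ml/min/1.73 m²).

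**The concern.** Lost contrast has opposite effects on the two kinds of test. In a difference test it shrinks the effect, and the likely result is a non-significant finding: power is lost and the error is conservative. In an equivalence test it moves the estimate toward zero, inside the margin, and so toward the claim that the trial hopes to make. The Discussion describes the first situation while the Analysis section names the second kind of test.

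At stake is a conclusion that deferral is equivalent to, or as safe as, routine start, drawn from arms that started at much the same eGFR. All-cause mortality is part of the primary endpoint, so an unsupported reassurance would matter. It would also repeat the weakness that the Background sees in the earlier trial.

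**Working it through.** **1. What the stated sample size represents.** Inputs from the Sample size section: "If we assume that alpha = 5%, (1-beta) = 80%, patients are assigned 1:1", a 30% death rate within 3 years, a 10-point difference and 30 months of enrolment. Three inputs are inferred or assumed: 20% in the other arm, a two-sided test, and exponential survival with a total duration of 3 years.

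- Hazard ratio = ln(0.80)/ln(0.70) = 0.626.
- Schoenfeld events = 4 × (1.960 + 0.842)² / [ln(0.626)]² ≈ 143. The protocol has 87 + 57 = 144.
- With these assumptions the event probabilities are 0.185 and 0.121. Times 473, they give 87.4 and 57.1 events, which matches 87 and 57.

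The stated figures therefore come from a test of difference under individual randomisation. They do not settle what happens under the equivalence test in the Analysis section.

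**2. Design effect.** The protocol's formula is DE = 1 + (m − 1)ρ, with ρ = 0.031 and 8 clusters per group.

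- m = 473/8 = 59.1, so DE = 1 + 58.1 × 0.031 = 2.80.
- The protocol's own event inflation is 198/144 = 1.375.

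These two values disagree, which is a separate issue. Both are carried forward as a range.

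**3. Chance of declaring equivalence.** Assumptions: a margin of 10 points (the only figure in the protocol that could serve as one); 473 per arm; equivalence declared if the 90% confidence interval lies within ±0.10; a true difference of 10 points under full separation (30% versus 20%); and dilution of that difference in proportion to the contrast lost. The arm at 30% stays fixed and the other drifts toward it.

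- SE = √{[p₁(1 − p₁) + p₂(1 − p₂)]/473 × DE}.
- Equivalence is declared if the absolute estimated difference is below c = 0.10 − 1.645 × SE.
- P(declare) = Φ[(c − d)/SE] − Φ[(−c − d)/SE], where d is the true difference that remains.

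Worked example, no contrast, DE 2.80: SE = √(0.42/473 × 2.80) = 0.0499; c = 0.10 − 0.082 = 0.018; P = 2Φ(0.36) − 1 ≈ 0.28.

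| Contrast retained | d | DE 2.80 | DE 1.375 |
|---|---|---|---|
| Full | 0.10 | 4.6% | 5.0% |
| Half | 0.05 | 20% | 43% |
| None | 0 | 28% | 78% |

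**4. Sensitivity.** Take event rates of 20% versus 30% or 30% versus 40%, with drift in either arm. The chance with all contrast lost is then 18–49% at DE 2.80 and 70–90% at DE 1.375. A 95% instead of a 90% interval lowers these to 0–26% and 53–81%. In the worked scenario at DE 2.80, the 95% interval gives only 1.5% with full contrast, about 5% with half and about 4% with none, because the interval is then almost too wide to fit within the margin at all.

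**The case against.** The strongest reply is that the protocol does not say which test governs. It sizes a log-rank difference and also plans Cox comparisons. If one of those carries the conclusion, the Discussion is right that convergence endangers power. This stands, and it makes the point conditional on the equivalence test being decisive.

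The wording of the Discussion is also guarded. The limitations say that convergence may happen, the implications are only potential, and nothing there states that equivalence will be claimed whatever the separation. That is fair. What remains is that the named consequence is wrong for the named test, and that arms with similar eGFR at start cannot inform about timing.

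Four stronger readings are tempting and are not supported:

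- A reader might infer that convergence would by itself produce a false finding of equivalence. At design effect 2.80, identical arms fail to show equivalence about 72% of the time (100% − 28%). Convergence biases toward the finding and can produce it; it does not guarantee it.
- An analysis that ignored clustering would give 53% with half the contrast and 91% with none. The Analysis section specifies a cluster-randomised test, so those figures do not describe this plan.
- A reader might infer that no adherence analysis or separation check is planned. The full protocol and the analysis plan are not shown and may contain them, so nothing here rests on their absence.
- Early symptomatic starts in the deferred arm might be counted as a fault. They follow the protocol and belong to the policy under comparison. Equivalence of the two policies as delivered could be true even when nothing has been learned about timing.

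The earlier trial's shrinkage cannot serve as a forecast either. Its early arm averaged 12, the midpoint of its planned 10–14, so the loss came from its late arm (9.8 against a planned 5–7). That is a different route from delay in the routine arm.

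**Conclusion.** The point holds in a limited form. Under the equivalence test in the Analysis section, convergence of eGFR at dialysis start pushes toward the positive conclusion, and the Discussion states the risk as lost power alone. Its expectation of new knowledge about timing is unsupported in the case where the arms do not separate.

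The direction follows from the type of test and needs no figures. The size is an illustration: from about 5% to between 28% and 78% with no contrast, depending on whether the design effect is 2.80 or 1.375. It rests on an assumed 10-point margin, a 90% interval, a true 10-point difference under full separation and proportional dilution. With a 95% interval at the larger design effect, the rise is small. The correction should be made, but the design itself is not invalidated.

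**What to change.** 1. State which test carries the primary conclusion: the equivalence test, or the Cox or log-rank difference test. If it is the equivalence test, correct the Discussion to say that convergence favours equivalence.
2. State in advance, before outcomes are compared by arm, a minimum between-arm difference in eGFR at dialysis start, set by the sponsor. If the achieved difference falls short, report the result as a comparison of the policies as delivered, and not as evidence that later timing is equivalent or safe. The visit schedule in Table 4 already includes eGFR at dialysis initiation. This value arises after randomisation and exists only for patients who start dialysis, so it should limit the wording of the conclusion and not select patients for analysis.
3. Beside the as-assigned analysis, report an adherence-based one. Censor patients when they depart from their arm's start rule for non-clinical reasons, and weight by the inverse probability of remaining uncensored. Symptomatic starts that follow the protocol are not departures. Claim equivalence of timing only if the two analyses agree. If the unshown analysis plan already has such an analysis, a cross-reference is enough.

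The cost is a change of wording, one case report form item for the reason dialysis was started, and one extra analysis. The downside is that the trial may have to report a more limited conclusion.

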## Data Availability

Not applicable.

## Abbreviations

AE: Adverse events
Alb: Albumin
AV: Arteriovenous fistulas
BNP: Brain natriuretic peptide
CBC: Complete blood count
CKD: Chronic kidney disease
CKD-EPI: Chronic kidney disease epidemiology collaboration
CONSORT: Consolidated standards of reporting trials
CRF: Case report form
CRO: Contract research organization
CRP: C reactive protein
DE: Design effect
DW: Dry weight
eGFR: Estimated GFR
ESKD: End stage kidney disease
GFR: Glomerular filtration rate
ICC: Intraclass correlation coefficient
IDEAL: The Initiating Dialysis Early and Late study
iPTH: Intact parathyroid hormone
KDOQI: Kidney disease outcomes quality initiative
NYHA: New York Heart Association
QOL: Quality of life
RADDI: Routine and deferred dialysis initiation
RCT: Randomized controlled trial
RRT: Renal replacement therapy
Scr: Serum creatinine
SD: Standard deviation
SGA: Subjective global assessment
SI: Serum iron
UCG: Ultrasound cardiography
UF: Ultrafiltration amount
UO: Urine output
